## Methods

### Study setting

This study protocol follows the SPIRIT 2013 (Standard Protocol Items: Recommendations for Interventional Trials) guidelines for reporting. The trial has been prospectively registered with the Clinical Trial Registry of India (CTRI/2025/03/084291). The study will be conducted after obtaining ethical clearance from the Institutional Ethics Committee at Datta Meghe Institute of Higher Education and Research (DMIHER), Sawangi (Meghe), Wardha, Maharashtra, India. Data collection will take place in the Respiratory Medicine Ward, Shalini Tai Meghe Superspecialist Centre, Sawangi, Wardha, Maharashtra.

#### Inclusion criteria

Adults aged 45–65 years of either sex.Patients who have undergone elective CABG surgery using a saphenous vein graft.Hemodynamically stable, conscious, and oriented patients within 1–10 days post-surgery.Participants who provide written informed consent.

#### Exclusion criteria

Hemodynamically unstable patients.Patients with neurological, or psychiatric disorders that interfere with rehabilitation participation.Patients with post-operative complications requiring re-intubation or prolonged ICU stay (>10 days).

### Sample size calculation

The sample size was calculated in consultation with the institutional biostatistician using Cohen’s formula for comparing two independent means (Cohen, 1988), assuming an effect size (d) = 0.49, α = 0.05, and power (1–β) = 0.80.

Parameter estimates were derived from previous studies with comparable rehabilitation protocols in post-CABG patients [10, 13], the estimated sample size was 35 participants per group. Allowing for a 20% dropout rate, the final sample size was adjusted to 42 participants per group, resulting in a total of 84 participants.

The chosen effect size of 0.49 represents a moderate clinical difference expected in primary outcomes such as functional capacity, scar healing, and quality of life. This sample size is therefore adequate to detect a meaningful difference between groups in early post-CABG recovery.

$$\mathrm{n}=\mathrm{d2}(2(\mathrm{Z}\upalpha /2+\mathrm{Z}\upbeta)2 \cdot (2{\upsigma}2))=35$$

Mean group 1 (M1): 5.53

Standard deviation group 1: 1.75

Mean group 2 (M2): 4.60

Standard deviation group 2: 2.00

Correlation between groups: 0.5 10

Effect size: 0.49

Alpha level: 0.05 Power (1-beta): 0.8

Sample size- 35 in each group

Drop out 20%= 20x35/100=7 35+7=42

The revised sample size is 42 in each group

The total sample size required = 84 subjects (42 subjects in each group)

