**Methods:**

A randomized controlled trial will be conducted at Shalini Tai Meghe Super Speciality Centre with 70 CABG patients aged 45–65 years. Participants will be randomly allocated to Group A (conventional physiotherapy) and Group B (leg cycle ergometry with physiotherapy) for a 10-day intervention. Outcome measures include the Vancouver Scar Scale, Manual Muscle Testing, 6-Minute Walk Test, and Patient Health Questionnaire-9 (PHQ-9). Data will be analysed using the Mann-Whitney U test and the Wilcoxon signed-rank test; p<0.05 was deemed statistically significant.

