### Recruitment

Subjects will be recruited through the Cardiovascular and Thoracic Surgery (CVTS) Intensive Care Unit and Ward, Shalini Tai Meghe Super speciality Centre, Sawangi (Meghe), Wardha, Maharashtra, India. Enrollment into the trial and baseline assessments will occur prior to the initiation of intervention. Eligible patients meeting the inclusion criteria will be approached within 24–48 hours of achieving hemodynamic stability following coronary artery bypass grafting. The purpose, procedures, potential benefits, and risks of the study will be clearly explained, and written informed consent will be obtained from all participants prior to recruitment.

Recruitment will continue until the required sample size of 84 participants (42 per group) has been achieved. The schedule of enrollment, intervention, and assessments is presented in Fig. 2.

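### The 35 per group does not follow from the stated two-independent-means calculation, which needs 67; the claimed 80% power is about 52% at 35 per group

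*Protocol article*

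**What the plan says.** The protocol's Sample size calculation section says the size was obtained "using Cohen’s formula for comparing two independent means (Cohen, 1988), assuming an effect size (d) = 0.49, α = 0.05, and power (1–β) = 0.80", and that "the estimated sample size was 35 participants per group". It lists means of 5.53 and 4.60, standard deviations of 1.75 and 2.00, "Effect size: 0.49", and a further input, "Correlation between groups: 0.5 10" (the trailing 10 looks like a reference number). Dropout is added as "Drop out 20%= 20x35/100=7 35+7=42". The section concludes: "This sample size is therefore adequate to detect a meaningful difference between groups in early post-CABG recovery".

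Elsewhere, Trial design specifies a 1:1 parallel-group trial. Statistical methods compares the groups by independent t-test or Mann–Whitney U test, with ANCOVA to adjust for baseline differences. The Abstract describes a trial "with 70 CABG patients aged" 45–65 years, whereas Recruitment says "Recruitment will continue until the required sample size of 84 participants (42 per group) has been achieved".

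**The concern.** A standardised difference of about 0.5 between two independent groups is well known to need a little over 60 per group for 80% power, so 35 is about half of what one expects. The listed correlation between groups points to the reason. Separately randomised patients are not matched, so no such correlation exists in this design. It is, however, a required input when the size is computed for paired measurements.

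The target size and the adequacy statement both rest on this calculation. If it is wrong, the trial claims a sensitivity that it does not have, and a non-significant result could be misread as coming from a trial with an 80% chance of detecting its planned effect.

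**Working it through.** **Inputs** (all from Sample size calculation): means 5.53 and 4.60, SDs 1.75 and 2.00, correlation 0.5, effect size 0.49, alpha 0.05 (two-sided, since the printed formula uses Zα/2), power 0.80.

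**1. The plan's effect size**
- Difference: 5.53 − 4.60 = 0.93.
- Independent groups: pooled SD = √[(1.75² + 2.00²)/2] = 1.879, so d = 0.93/1.879 = 0.495.
- Paired, with r = 0.5: SD of the difference = √(1.75² + 2.00² − 2 × 0.5 × 1.75 × 2.00) = 1.887, so dz = 0.93/1.887 = 0.493.

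At r = 0.5 the two effect sizes nearly coincide. The value 0.49 alone therefore does not show which design was used; the resulting n does.

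**2. Trying to reproduce 35**

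| Calculation, 80% power | n |
|---|---|
| Independent means, d = 0.49, normal: 2(1.960 + 0.842)²/0.49² = 65.4 | 66 per group |
| Independent means, d = 0.49, exact t: 66.4 | 67 per group |
| Independent means, d = 0.495 | 65 (normal) or 66 (t) per group |
| Independent means, d = 0.49, one-sided | 52 (normal) or 53 (t) per group |
| ANCOVA, assumed baseline–outcome correlation 0.5, normal | 50 per group |
| Printed formula read literally, with both factors of 2 | about 131 per group |
| **Paired t-test, 0.49, exact t: 34.7** | **35 pairs in total** |

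Only the paired calculation gives 35. Its power is 80.4% with 35 pairs and 79.2% with 34.

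**3. Power of the planned two-group comparison** (d = 0.49, two-sided 0.05, exact t, unadjusted)
- 35 per group: 52.4%
- 42 per group, no dropout: 60.2%
- 42 × 0.8 = 33.6 per group after 20% loss: 50.8%

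**4. Effect detectable with 80% power**
- 35 per group: d = 0.68, which is 0.68 × 1.88 = 1.28 on the scale of the listed means
- 42 per group: d = 0.62

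**5. Gain from ANCOVA** (assumed baseline–outcome correlation 0.5; the protocol gives none)
- 35 per group: 65%
- 42 per group: 73%
- Correlation needed for 80% power: about 0.7 at 35 per group, about 0.61 at 42

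**6. Dropout**
- Adding 20% of 35 gives 42, and 42 × 0.8 = 33.6, which is below 35.
- Retaining 35 after 20% loss needs 35/0.8 = 43.75, i.e. 44 per group.
- 42 per group tolerates 1 − 35/42 = 16.7% loss.

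**7. Other figures that disagree**
- The Abstract's 70 equals 2 × 35, apparently the size before dropout; Sample size calculation and Recruitment give 84.
- Sample size calculation lists quality of life among the primary outcomes. Outcome measures names two co-primaries (Vancouver Scar Scale and 6-Minute Walk Test) and makes quality of life secondary.
- The outcome behind 5.53 and 4.60 is not named. Such values are not plausible six-minute walk distances in metres.

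**The case against.** The protocol never says that a paired calculation was used. That is an inference, though a strong one: a listed input that only a paired calculation needs, and an exact match at 35. The error does not depend on it, because the stated method with the stated inputs does not give 35.

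The 52% is one scenario. The trial recruits 42 per group, and Statistical methods plans intention-to-treat with last observation carried forward, so up to 42 per group might be analysed. That gives 60%, provided imputation does not dilute the effect. ANCOVA could raise it to 73% under the assumed correlation of 0.5. In the other direction, the Mann–Whitney U test, the only between-group test that the Abstract names, gives about 51% at 35 per group under normality. The range is fair, but none of these figures reaches 80%. The ANCOVA gain also needs a correlation that the protocol does not supply.

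It would be too strong to say that the 6-Minute Walk Test has no power basis at all, since the section applies the standardised 0.49 to functional capacity too. What stands is that the source outcome is unnamed and 0.49 is carried over to walking distance without support.

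The dropout slip is small (50.8% against 52.4%), and the 70/84 and quality-of-life conflicts are editorial. They do not add to the weight of the main point. The Discussion's mention of a small sample as a limitation does not correct the 80% claim.

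**Conclusion.** The concern holds. For two independent means at d = 0.49, two-sided alpha 0.05 and 80% power, the requirement is 67 per group, 134 evaluable in total. The stated 35 is reproduced only as the number of pairs in a paired t-test, a design this trial does not have. Unadjusted power for the planned effect is 52% at the plan's own 35 evaluable per group, and runs from 51% (20% loss from 42) to 60% (no loss). These figures assume a t-test on one endpoint with a true d of 0.49. The conclusion that power falls short of 80% survives the favourable ANCOVA case at an assumed correlation of 0.5. The adequacy statement is wrong as written and must be corrected.

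**What to change.** Keep 84 patients and correct the Sample size calculation section:

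- Delete the correlation between groups and the sentence calling the size adequate.
- State about 52% power for d = 0.49 with 35 evaluable per group, and 80% power for d = 0.68 (0.62 with 42). Any gain claimed from ANCOVA should be given with its assumed correlation.
- State that 42 per group leaves 35 after 16.7% dropout, and 33.6 after 20%; keeping 35 after 20% loss would need 44.
- Name the outcome and source behind 5.53 and 4.60. Add the detectable 6-Minute Walk Test difference, using an SD that the sponsor supplies, since the protocol gives none.
- Remove quality of life from the primary outcomes listed there, and change the Abstract from 70 to 84.

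This costs protocol wording only and adds no patients, but the stated power becomes less favourable. The alternative, if the sponsor wants 80% power at d = 0.49 without adjustment, is 67 evaluable per group: 67/0.8 = 83.75, so 84 per group and 168 in total. That doubles recruitment, which Trial status shows running from June 2025 to August 2026. The choice is the sponsor's; the current claim cannot stand under either option.

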#### Outcome measures

All outcomes will be assessed at two time points: baseline (post-operative day 1–2, before intervention) and at the end of the 10-day Phase I rehabilitation period (post-operative day 10). Assessments will be conducted by blinded physiotherapists in the hospital setting.

This trial has two co-primary outcomes: (1) scar healing measured by the Vancouver Scar Scale and (2) functional capacity measured by the 6-Minute Walk Test. Secondary outcomes include muscle strength (MMT) and quality of life (PHQ-9).

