#### Primary outcome measures

Scar Healing (Vancouver Scar Scale): The Vancouver Scar Scale assesses four scar parameters—height, pliability, pigmentation, and vascularity—each scored to yield a total of 0–13, where higher scores indicate greater impairment. It is one of the earliest validated clinical tools for objective evaluation of post-surgical scars and is sensitive to short-term healing responses in hospital settings.Functional Capacity (6-Minute Walk Test): The 6MWT is a standardized sub-maximal exercise test that evaluates aerobic capacity and endurance. The total distance walked in six minutes reflects overall cardiopulmonary fitness. It is widely recommended in cardiac rehabilitation guidelines (AHA/ESC) for assessing early functional gains in post-CABG patients

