## Discussion

Coronary artery bypass grafting remains one of the most performed and effective revascularization procedures, yet donor-site complications from saphenous vein harvesting such as edema, pain and delayed scar healing can significantly restrict early mobility and delay recovery. Early rehabilitation and mobilization are vital to reduce postoperative functional decline and improve hospital outcomes. Leg cycle ergometry, a closed chain rhythmic exercise, can enhance venous return, improve peripheral circulation, and maintain muscle activation without imposing excess cardiac stress. Incorporating LCE during Phase I cardiac rehabilitation may therefore promote graft site healing, preserve lower limb strength and accelerate functional independence. The selected outcome measures—Vancouver Scar Scale (VSS), 6-Minute Walk Test (6MWT), Manual Muscle Testing (MMT), and PHQ-9—collectively capture the multidimensional nature of recovery. VSS evaluates donor site tissue integrity, 6MWT and MMT reflect physiological and functional capacity, while PHQ-9 captures short-term psychological well-being that influences adherence to rehabilitation. Earlier studies, such as those by Hirschhorn et al. [13] and Hamid et al. [10], demonstrated the safety and feasibility of early ergometry in CABG patients but did not assess localized donor-site outcomes or psychological domains. Hence, this trial addresses an important evidence gap by integrating lower-limb-specific intervention and comprehensive outcome evaluation within the early post-CABG recovery phase, especially in an Indian tertiary-care setting where structured Phase I cardiac rehabilitation is still developing.

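### The planning effect of 0.49 comes from one pair of means on an unnamed scale, and on the protocol's own account it is tied to neither co-primary outcome

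*Protocol article*

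**What the plan says.** Sample size calculation gives d = 0.49, alpha 0.05 and power 0.80, and names its method as a "formula for comparing two independent means". On the origin of the inputs it says: "Parameter estimates were derived from previous studies with comparable rehabilitation protocols in post-CABG patients [10, 13". The inputs are printed as a list beginning "Mean group 1 (M1): 5.53", followed by SD 1.75, then a second mean of 4.60 with SD 2.00, and a correlation of 0.5. No instrument, unit or time point is attached to any of them. The result is 35 per group, raised to 42 per group (84 in total) for dropout.

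The section then interprets the number: "The chosen effect size of 0.49 represents a moderate clinical difference expected in primary outcomes such as functional capacity, scar healing, and quality of life". It concludes from this that the size suffices to detect a meaningful difference.

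Three other places bear on this:

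- **Discussion**, on references 13 and 10: they showed early ergometry to be safe and feasible, "but did not assess localized donor-site outcomes or psychological domains".
- **Outcome measures**: VSS and 6MWT are the two co-primary outcomes. "Secondary outcomes include muscle strength (MMT) and quality of life (PHQ-9").
- **Primary outcome measures**: VSS totals run from 0 to 13. For the 6MWT, "The total distance walked in six minutes reflects overall cardiopulmonary fitness".

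**The concern.** A standardised effect may be chosen by convention, and then it needs no source. This protocol does something different. It says that its effect was derived from data in two cited studies and that it is the difference to be expected in three named domains. The Discussion's account of those same studies removes two of the three domains, and the size of the printed means makes the third doubtful.

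What is at stake is the justification for the size of the trial. The statement of adequacy is the only one that the article offers, and it rests on an effect that cannot be traced to scar healing or to walk distance. A reader cannot tell what difference, in VSS points or in metres, the trial was planned to find. The mention of quality of life as a primary outcome is a smaller inconsistency in the same sentence.

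**Working it through.** **1. Reproduce the 0.49.** Inputs, all from Sample size calculation: means 5.53 and 4.60, SDs 1.75 and 2.00, correlation 0.5.

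- Difference: 5.53 − 4.60 = 0.93.
- Pooled SD: √((1.75² + 2.00²)/2) = 1.879, so d = 0.93/1.879 = 0.495.
- SD of a paired difference at r = 0.5: √(1.75² + 2.00² − 2 × 0.5 × 1.75 × 2.00) = 1.887, so dz = 0.93/1.887 = 0.493.

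Either route gives the stated 0.49 to within rounding. The figure is thus one contrast on one scale, not a summary over three outcomes.

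**2. Ask which outcome the means could belong to.**

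| Outcome | Status in Outcome measures | Do 5.53 and 4.60 fit the scale? | Could references 10 and 13 supply it, by the protocol's own account? |
|---|---|---|---|
| VSS, 0–13 | co-primary | yes, numerically | no: the Discussion says donor-site outcomes were not assessed |
| 6MWT, distance | co-primary | not credible in metres | not excluded, but the values do not fit |
| PHQ-9 | secondary | yes, numerically | no: the Discussion says psychological domains were not assessed |
| Manual muscle test, grades 0–5 | secondary | 5.53 exceeds a single grade | not excluded, but 5.53 does not fit unless grades were summed |

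The scales that fit are those that the Discussion rules out. The scales that it leaves open do not fit in their usual units.

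**3. What the planned number can detect.** This is for an independent two-sample t-test, two-sided alpha 0.05, power 0.80. The normal approximation is d = (1.960 + 0.842) × √(2/n). The noncentral t distribution gives slightly larger values.

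| Analysed per arm | Normal approximation | Noncentral t |
|---|---|---|
| 35 | 0.67 | 0.68 |
| 42 | 0.61 | 0.62 |

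**4. Keep the formula error apart.** The stated independent-means method at d = 0.49 needs 2 × (1.960 + 0.842)²/0.49² = 65.4, so 66 per arm (67 by noncentral t). The figure of 35 appears only as the number of pairs in a paired t-test with dz = 0.49. That is why 0.62 to 0.68 differs from 0.49. It is a different defect: correcting it would leave the effect size just as unconnected to VSS and 6MWT.

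**5. Illustration in metres.** The protocol gives no SD for walk distance. If it lay between 60 and 100 m (an assumption), the detectable difference would be 0.62 × 60 = 37 m to 0.62 × 100 = 62 m with 42 per arm, and 0.68 × 60 = 41 m to 0.68 × 100 = 68 m with 35 per arm. No VSS equivalent can be given without an SD in points.

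**The case against.** **The Discussion sentence is loose narrative about studies not seen here.** The Introduction credits reference 10 with better self-efficacy in daily activities, which is arguably a psychological construct, so the article's account of that reference is not uniform. Either section could be the one in error. This stands. A reader might infer that the means cannot be VSS, PHQ-9 or walk values. The documents do not support that: 5.53 and 4.60 lie within the VSS range, no unit is printed, a rescaled distance is not strictly excluded, and functional capacity in a source study could have been another measure. What they do support is a conflict between two sections that has to be reconciled. A different functional measure would still leave the link to the 6MWT unexplained.

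**A standardised effect needs no unit, and an article condenses.** This would hold for a conventional d. It does not answer a printed claim that the d was derived from data and is expected in named outcomes. A fuller document could supply the unit, but it could not make both sections true as they stand.

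**The quality-of-life wording is a slip.** Largely so. It sits in an illustrative phrase, while the outcome sections define primary and secondary clearly. A reader might infer that PHQ-9 could later be reported as primary, but those definitions make that risk slight.

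**Interpretation of results is not lost.** A reader might infer that a null or a significant result could not be interpreted. That does not follow. The confidence interval, read against a relevance threshold, governs both, whatever d was used for planning.

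**Conclusion.** The concern holds in this form: as the article stands, the planning effect is not tied to either co-primary outcome, and the claim that 0.49 is expected in scar healing, functional capacity and quality of life is contradicted or unsupported for each. The statement that the size is adequate therefore lacks a basis for VSS and for 6MWT.

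The conflict between Sample size calculation and Discussion is a matter of record. That the means are not walk distances is an inference, which assumes metres. The detectable differences (about 0.62 with 42 analysed per arm, about 0.68 with 35) assume an unadjusted two-sample t-test at two-sided 5% for each outcome. They show what the planned number can do and do not measure this defect, since their distance from 0.49 comes from the formula error. The point should be corrected, but it does not call for a redesign.

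**What to change.** 1. In Sample size calculation, name the instrument, unit and source behind 5.53 and 4.60, and bring this into line with what the Discussion says about references 10 and 13.
2. Delete the claim that 0.49 is the expected effect on all three outcomes, unless a source supports it for each one.
3. Replace the adequacy statement with the difference that the planned number can detect at 80% power on each co-primary: standardised d of about 0.62 with 42 analysed per arm and about 0.68 with 35. Convert these to VSS points and metres with a sourced SD. Label them as detectable differences. A value worked back from a fixed sample size is not a clinically meaningful difference and should not be presented as one.
4. Remove quality of life from the primary outcomes in that section, so that it agrees with Outcome measures.

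The cost is a protocol wording change and a short recalculation, with no extra patients. Recruitment is reported to have begun in June 2025, so the change should be dated and recorded as an amendment. The downside is a less favourable stated justification.

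### The 20% dropout allowance is added to 35 rather than divided out, so 42 per group leaves fewer than 35 after a 20% loss

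*Protocol article*

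**What the plan says.** The Sample size calculation section of the Protocol article sets the base requirement: "the estimated sample size was 35 participants per group". It then applies the allowance in prose, "Allowing for a 20% dropout rate, the final sample size was adjusted to 42 participants per group", and prints the working: "Drop out 20%= 20x35/100=7 35+7=42". It concludes: "The total sample size required = 84 subjects (42 subjects in each group".

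The Recruitment section makes that figure operative: "Recruitment will continue until the required sample size of 84 participants (42 per group) has been achieved".

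The prose, the printed working and the recruitment target agree with one another. Nowhere does the article define the 20% in another way, for example as a percentage of completers, and nowhere does it divide by 0.80.

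**The concern.** A dropout allowance exists so that, if the assumed fraction of randomised patients is lost, the number left still meets the requirement. The fraction therefore applies to the number randomised. The plan takes 20% of the number it wants to have left and adds that. This always gives too few, because the patients added are themselves subject to the same loss.

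What is at stake is whether three stated figures can all be true: 35 needed, 20% lost, 42 recruited. If they cannot, the figure that decides when recruitment stops does not deliver what the plan says it needs.

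**Working it through.** **Inputs**, all from the Protocol article, Sample size calculation:

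- required number per group, n = 35
- dropout rate, r = 20%
- number recruited per group, N = 42 (84 in total, repeated under Recruitment)

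**1. Reproduce the plan's figure.** n x (1 + r) = 35 x 1.20 = 42. This matches exactly, so the method used is not in doubt.

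**2. Apply the stated loss to the stated target.** N x (1 - r) = 42 x 0.80 = 33.6 per group, or 84 x 0.80 = 67.2 in total. The plan needs 35 per group, 70 in total. The expected shortfall is 35 - 33.6 = 1.4 per group.

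**3. Find the loss that 42 covers.** (42 - 35)/42 = 7/42 = 16.7%.

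**4. Find the number that covers 20%.** n/(1 - r) = 35/0.80 = 43.75, rounded up to 44 per group, 88 in total. Check: 44 x 0.80 = 35.2. The gap is two per group and four overall.

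**5. Chance of missing the requirement.** Assume that each patient independently has a 20% chance of dropping out. The probability that a given group ends with fewer than 35 completers is then about 0.62 with 42 randomised and about 0.38 with 44.

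**6. Effect on power** (t-test, standardised effect 0.49, two-sided 5%). The formula in the plan uses Z at alpha/2, so two-sided is the natural reading. The value at 33.6 treats n as continuous.

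| Calculation | n = 35 | n = 33.6 |
|---|---|---|
| Paired comparison, n pairs | 0.804 | 0.787 |
| Two independent groups, n per group | 0.524 | 0.508 |

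Both rows are shown because the base figure does not come from the method the plan names. The plan describes the calculation as "using Cohen’s formula for comparing two independent means (Cohen, 1988" and states its assumptions as "assuming an effect size (d) = 0.49, α = 0.05, and power (1–β) = 0.80". For two independent means those assumptions need 66 per group by the normal approximation, or 67 by the t-test. The figure of 35 is what a paired calculation gives with the printed means (5.53 and 4.60), standard deviations (1.75 and 2.00) and correlation (0.5):

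- SD of the difference = sqrt(1.75² + 2.00² - 2 x 0.5 x 1.75 x 2.00) = 1.887
- paired effect size = (5.53 - 4.60)/1.887 = 0.493
- power with 35 pairs = 0.808

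**7. The same step on a larger base.** With 66 per group, adding 20% gives 79.2, so 80, while dividing gives 66/0.80 = 82.5, so 83. With 67 the two figures are 81 and 84. The shortfall grows with the base.

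**The case against.** The arithmetic is hard to dispute. The case on the other side is about its weight and its remedy.

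- **The size is negligible.** The loss is 1.4 expected patients per group, and power moves by less than two percentage points on either calculation. No source is given for the 20%, so the distance between 16.7% and 20% lies within the uncertainty of the assumption. This stands as a judgement of size. It does not make the stated figures agree.
- **Dropouts may stay in the analysis.** The plan does not say that the 35 must be completers. The Statistical methods section takes an intention-to-treat approach with last observation carried forward where appropriate, so patients with only a baseline value could still be counted, up to all 42. This helps only in part. With two assessments, the value carried forward is the baseline, which is not an observed outcome, and the rule is conditional. The plan also chose to inflate for dropout, and that only makes sense if dropouts are expected to cost information.
- **The working is open.** A reader can see that the allowance is seven patients. That is true, and it makes the error easy to correct, but recruitment still follows the resulting total.
- **The base of 35 is the larger problem, and moving to 88 could mislead.** This stands. With all 44 per group analysed, power for the between-group comparison at 0.49 is about 0.62; with the 35 left after a 20% loss it is about 0.52. The figures 44 and 88 are right only conditionally on a base of 35.

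**Conclusion.** The concern holds. Taking 35 as the requirement and 20% as the proportion of randomised patients lost, 42 per group is not enough: the expected number remaining is 33.6, and 42 protects against 16.7% loss. The matching figure is 44 per group, so the plan is short by two per group and four in total (84 against 88).

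The practical effect is slight, and this step alone would not change the trial's conclusions. It still deserves correction, because a stated figure that governs when recruitment stops is wrong as written, and because the same method would carry a larger shortfall into any revised target. The conclusion rests on the ordinary meaning of a dropout rate and on the plan's own numbers. It does not depend on whether 35 is right, and correcting it does not make 35 right.

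**What to change.** Preferred: keep 84 and correct the statement, for example: 42 per group retains 35 per group if up to 16.7% of randomised participants are lost. This costs one line and no patients.

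If the sponsor wishes to keep a 20% allowance on a base of 35, the consistent figures are 35/0.80 = 44 per group and 88 in total, which is four more patients. This should not be presented as making the sample size adequate for the between-group comparison.

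In either case, if the base is recalculated, obtain the number to randomise by dividing by one minus the dropout rate and rounding up, and carry the result into the Recruitment section. The article expects recruitment to finish in August 2026; if it is still open, the target can be changed, and the wording can be corrected at any time.
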